### Sample size {14}

Our conservative sample size and power calculations for the primary outcomes, which constitute a family of hypotheses [63], assume a two-sided overall family-wise error rate of 0.05 [64], 80% power, an analysis of covariance (ANCOVA)-based approach, and an attrition rate of 25% with 82 participants finishing the study. Under these assumptions, we will have 80% power to detect at least a minimally detectable difference (Cohen’s *d*) of 0.552. In these calculations, a conservative correlation of 0.6 between the baseline covariate and outcome is assumed, which is similar to a previous study by Froehlich-Grobe et al. [4].

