## Statistical methods

### Statistical methods for primary and secondary outcomes {20a}

#### Primary analysis

The primary analysis for the average treatment effect (**primary aim**) will employ an intent-to-treat linear mixed model ANCOVA with the baseline outcome measures as covariates, the corresponding post-intervention outcome measures as the dependent variables, the intervention as the main factor, and the intervention waves as random effect. In general, missingness will be handled by our choice of mixed models to handle the multi-level data. Mixed models use all the data available to directly estimate model parameters via maximum likelihood or restricted maximum likelihood. Where necessary, we will supplement these primary analyses by using multiple imputation procedures with 10 imputations [4]. We have configured three families of hypotheses based on our primary and secondary outcomes.

For the **secondary aim**, we will estimate the effect sizes and their 95% confidence intervals and compare them with the corresponding effect sizes and interval estimates from a previous M2M trial [65]. We will generate 95% percentile bootstrap confidence intervals between the differences in the effect sizes utilizing data from both trials. To test for pre-specified moderators, we will extend our models in the primary aim to include moderators as main effects along with an interaction term with the intervention. A test for interaction between the moderator and intervention will be conducted.

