### Methods in analysis to handle protocol non-adherence and any statistical methods to handle missing data {20c}

Missing data will be imputed using multiple imputation where necessary, with assumption that the missingness mechanism is missing at random.

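### Ten imputations are few for 25% planned attrition: a borderline multiple-imputation p-value would depend noticeably on the random seed, although the primary mixed-model p-value would not

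*Protocol article*

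**What the plan says.** Under Primary analysis (Statistical methods for primary and secondary outcomes {20a}), the trial "will employ an intent-to-treat linear mixed model ANCOVA with the baseline outcome measures as covariates", with the post-intervention value as dependent variable and wave as a random effect. On missing data the section first says that "missingness will be handled by our choice of mixed models to handle the multi-level data", and explains that "Mixed models use all the data available to directly estimate model parameters via maximum likelihood or restricted maximum likelihood". It then adds: "Where necessary, we will supplement these primary analyses by using multiple imputation procedures with 10 imputations".

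The section on non-adherence and missing data {20c} returns to the subject: "Missing data will be imputed using multiple imputation where necessary, with assumption that the missingness mechanism is missing at random". Unlike Primary analysis, with its "multiple imputation procedures with 10 imputations", it gives no number of imputations, and it does not repeat that imputation is only a supplement. Neither section says what would make it necessary.

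Sample size {14} plans for 25% attrition, with 82 participants finishing, a two-sided family-wise error rate of 0.05, a baseline-outcome correlation of 0.6 and a detectable Cohen's d of 0.552. It prints no per-test threshold. Outcomes {12} has one measurement after baseline, at 12 weeks.

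**The concern.** The number of imputations is printed in the plan, so it can be judged against the plan's own expected missingness. Ten is often defended by relative efficiency, which is indeed high here. But relative efficiency describes how much precision is lost on average. It does not describe how far the pooled test statistic moves when the same data are imputed again with another seed.

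A supplementary analysis is there to show whether the primary result is robust. If its p-value can fall on either side of the threshold by chance of seed, a reader cannot tell real sensitivity to missing data from Monte Carlo noise. Because the section on missing data {20c} does not confine imputation to a supplementary role, the noise would matter more if an imputation result were ever given more weight.

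**Working it through.** **Inputs.** From the article: 108 randomised; 82 finishing, so 108 − 82 = 26 missing (26/108 = 24.1%); correlation 0.6; 10 imputations; family-wise alpha 0.05; d = 0.552. Assumed: 1:1 allocation, a fraction of missing information (FMI) of about 0.25 (range 0.15 to 0.35 shown), and no wave effect in the simulation.

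**1. Which per-test threshold fits the plan's own figure.** With ANCOVA the residual SD is √(1 − 0.6²) = 0.8. The detectable difference is d = (z₁₋α/₂ + z₀.₈₀) × 0.8 × √(4/82).

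| Per-test alpha | d, normal | d, noncentral t |
|---|---|---|
| 0.05 | 0.495 | 0.501 |
| 0.025 | 0.545 | 0.554 |
| 0.0167 | 0.572 | 0.582 |

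For 0.025 the normal formula reads (2.241 + 0.842) × 0.8 × 0.2209 = 0.545. The stated 0.552 lies between the two values for 0.025 and outside the other rows, so 0.025 is used below. It remains an inference.

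**2. Efficiency.** Relative efficiency = 1/(1 + FMI/m) = 1/(1 + 0.25/10) = 0.976. The average loss is about 2.4%.

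**3. Monte Carlo error, analytic.** The Monte Carlo error of the pooled estimate, relative to its standard error, is √(FMI/m).

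- m = 10: √(0.25/10) = 0.158. Around z = 2.241 (p = 0.025), the 95% range is 2.241 ± 1.96 × 0.158, or 1.93 to 2.55, giving p from 0.053 down to 0.011.
- m = 100: √(0.25/100) = 0.05. The range is 2.14 to 2.34, giving p from 0.032 down to 0.019.
- At m = 10 the range of p is 0.013-0.045 with FMI 0.15 and 0.009-0.061 with FMI 0.35. All of these straddle 0.025.

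This counts only noise in the estimate. The pooled standard error and its degrees of freedom also vary between seeds, so simulation gives a wider spread.

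**4. Simulation.** N = 108, 26 outcomes missing (13 per arm), correlation 0.6. The 12-week value is imputed from arm and baseline and pooled by Rubin's rules with Barnard-Rubin degrees of freedom. The data set is held fixed and only the seed changes, with 1,500 runs per setting. The FMI came out at about 0.25.

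| p on observed data | m = 10: 95% range of p | m = 10: share below 0.025 | m = 100: 95% range of p | m = 100: share below 0.025 |
|---|---|---|---|---|
| 0.005 | 0.001-0.024 | 98% | 0.004-0.008 | 100% |
| 0.010 | 0.003-0.038 | 89% | 0.007-0.015 | 100% |
| 0.015 | 0.005-0.052 | 74% | 0.011-0.022 | 99.8% |
| 0.020 | 0.007-0.061 | 56% | 0.015-0.029 | 85% |
| 0.025 | 0.010-0.074 | 39% | 0.019-0.035 | 41% |
| 0.030 | 0.011-0.084 | 28% | 0.023-0.042 | 7% |

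A separate simulation of the same set-up gives an SD of t across seeds of about 0.22 at m = 10 and 0.07 at m = 100. This is the expected ratio, since 0.22/√10 = 0.07. For an observed-data p of 0.02, its 5-95% range of p is 0.009-0.056 at m = 10 and 0.016-0.028 at m = 100.

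**The case against.** The strongest reply is that imputation does not carry the primary result. A reader might infer from these figures that the trial's significance call is not reproducible. The article does not support that: the primary analysis is fitted by maximum or restricted maximum likelihood, which involves no random draws, and nothing in the article takes the decision from imputed data. This part of the objection stands in full.

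A reader might also argue that, with a single post-baseline measurement, imputation is the only step that brings non-completers into an intent-to-treat result. It is true that the model as described gains essentially nothing from someone without a 12-week value. But when the imputation uses only arm and baseline, as in the check above, it adds no outcome information either and scatters around the observed-data ANCOVA. Whether imputation should have a larger role is a different question from how many imputations to run.

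Three further limits stand. The instability is confined to borderline results. The 25% is a planning rate, and 0.025 is inferred. A fixed seed would make any number of imputations exactly repeatable, and its absence here is no fault, because a seed is commonly left to the analysis plan. But a seed makes a noisy result repeatable without making it less arbitrary; only more imputations reduce the noise.

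**Conclusion.** The point holds in a narrow form and is minor. If about a quarter of outcomes are missing, 10 imputations leave the imputation p-value with enough seed noise to cross a 0.025 threshold when the observed-data p is near it: at 0.02, only 56% of seeds fall below 0.025, against 85% with 100 imputations. At 0.005, 98% already do so with 10. The consequence is that disagreement between a borderline primary result and its imputation supplement could not be read as evidence about missing data.

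This rests on 1:1 allocation, FMI near 0.25, the inferred per-test threshold, and a simulation without the wave effect. The straddling of 0.025 at m = 10 persists for FMI from 0.15 to 0.35.

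**What to change.** In Primary analysis, replace 10 imputations with at least 100, and let that number apply also to the imputation described in the section on missing data {20c}. The only cost is computing time; design, participants and power are untouched. The larger number cuts the Monte Carlo SD of t to about a third. It does not remove the noise for a p-value lying at the threshold itself, where about 41% of seeds still fall below 0.025.

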#### Secondary analysis

Based on the *p* values for all the analyses reported, we will report the false discovery rate and false discovery proportion. We will estimate Bayes factor for each comparison, which is especially useful in the interpretation if the null is not rejected. Using the outcome data, we will conduct exploratory cluster analysis to assess whether the clustering occurs based on functional level or disability type. Descriptive comparisons of *e*M2M effects between disability groups will be reported where appropriate. We will examine barriers in physical activity as well as the four Social Cognitive Theory constructs: self-efficacy, goal-setting, outcome expectancies, and social support as mediating variables between the intervention and the outcomes using the product of coefficients test as suggested by Mackinnon and colleagues [26].

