### Objectives {7}

The movement-to-music (M2M) study aims to examine a rhythmic-based teleexercise intervention (eM2M) with 108 adults with physical disabilities. Specifically, the **primary aim** is to investigate effects of the 12-week eM2M intervention on physical and psychosocial health outcomes in participants who are classified into three functional mobility groups: Group I—only able to exercise while sitting, Group II—able to exercise sitting and standing with or without support, and Group III—able to exercise one side of the body more than the other side. We hypothesize that participants who receive the 12-week eM2M intervention will have the following:
Significantly higher gains in cardiorespiratory fitness and muscle strength compared to waitlist control (*WC*) participants post-intervention.Significantly greater gains in lower extremity function, physical activity, health-related quality of life, and social participation compared to *WC* participants post-intervention.

The **secondary aim** is to compare the effect sizes of eM2M on physical health outcomes including cardiorespiratory fitness, muscle strength, and lower extremity function with those observed in a previous M2M trial [26] that grouped participants based on disability type. We hypothesize that gains in physical health will be larger than in the previous M2M trial where participants were grouped by disability type.

The **tertiary aim** is to explore the role of group cohesion, instructor support, exercise self-efficacy, exercise self-regulation, social support for exercise, and outcome expectations for exercise as mediating variables between eM2M and the primary and secondary outcomes. The heterogeneity of treatment effect across the physical health outcomes will also be examined using functional mobility and disability type as moderators.

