### Interventions

Enrolled participants who complete baseline assessments will be randomly assigned to *eM2M* or *WC*. After randomization, participants in the *eM2M* arm will meet virtually with study staff who will provide information about the intervention schedule and an online program (e-STORIES) [29] on exercise self-regulation strategies, including goal setting, to be completed prior to beginning the intervention. Participants in *WC* will be instructed to maintain their usual activities during the 12-week intervention and will be invited to participate in an eM2M program after the control period. Both *eM2M* and *WC* participants will be asked to complete a weekly electronic survey on their physical activity level.

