### Outcomes {12}

Primary and secondary outcomes include a set of physical assessments and self-report questionnaires and will be assessed at baseline and post 12-week intervention via the Zoom platform (teleassessments [34]) and REDCap electronic questionnaires. Assessors will be blinded to participant assignment, and allocation of the arm assignment will not be done until baseline testing is completed. The outcome measures included in this study were developed and validated in previous literature with adequate to excellent reliability. The primary outcomes include changes in cardiorespiratory fitness measured with resting heart rate [35] and the heart rate recovery test [36, 37] as well as muscle strength assessed with hand-held dynamometer [38–40] at post 12-week intervention. The secondary outcomes include changes in lower extremity function assessed with the Short Physical Performance Battery [41] and the Timed Up and Go tests [42–44], health-related quality of life measured using the NIH PROMIS 10 Global Health Items [45], social participation measured using the NIH PROMIS Ability to Participate in Social Roles and Activities Short Form 8a [45], and physical activity measured using the Godin Leisure Time Exercise Questionnaire [46–54] at post 12-week intervention. Table 2 summarizes all outcome measures and the corresponding data collection time points.

**Table 2 Tab2:** Outcome measures of the M2M study

Role	Variables	Outcome measures	Collection time points
**Primary outcomes**	Cardiorespiratory fitness	Resting heart rate [35] Heart rate recovery test [36, 37]	Baseline and 12 weeks
	Muscle strength	Hand-held dynamometer [38–40]	Baseline and 12 weeks
**Secondary outcomes**	Lower extremity function	Short physical performance battery [41] Timed up and go [42–44]	Baseline and 12 weeks
	Health-related quality of life	NIH PROMIS 10 Global Health Items [45]	Baseline and 12 weeks
	Social participation	NIH PROMIS Ability to Participate in Social Roles and Activities Short Form 8a [45]	Baseline and 12 weeks
	Physical activity	Godin Leisure Time Exercise Questionnaire [46–54]	Baseline and 12 weeks
**Mediators**	Program adherence	Percentage of # of attended eM2M sessions	12-week intervention period
	Group cohesion	Physical Activity Group Environment Questionnaire [55–57]	12 weeks
	Instructor support	Perceived Autonomy Support Scale for Exercise Settings [57, 58]	12 weeks
	Exercise self-efficacy	Exercise Self-efficacy Scale [59]	Baseline and 12 weeks

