	Exercise self-regulation	Exercise Goal-setting Scale [60]	Baseline and 12 weeks
	Outcome expectations for exercise	Multidimensional Outcome Expectations for Exercise Scale [61]	Baseline and 12 weeks
	Social support for exercise	Social Provisions Scale [62]	Baseline and 12 weeks
**Moderators**	Functional mobility	Short Physical Performance Battery [41]	Baseline
	Disability type	Demographics and Health History Questionnaire	Baseline
**Covariates**	Barriers in physical activity	Barriers in Physical Activity Questionnaire [63]	Baseline

In addition, after participants complete the eM2M intervention, they will be asked to participate in semi-structured interviews via Zoom. The interviews will be conducted in a group format (the same group of participants that underwent the intervention together). The interviews will include questions that probe participants’ perceived impact of eM2M on their health and function, as well as their experience exercising with other participants with similar functional levels who have different disabilities. The interviews will be audio-recorded, transcribed, and analyzed using a latent thematic analysis approach (underpinned by interpretivism).

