### Data collection and management

#### Plans for assessment and collection of outcomes {18a}

Before conducting the baseline teleassessments, study staff will connect with each participant for a virtual home visit via Zoom using the laptop mailed to them. The purpose of this visit is to walk participants through all provided testing equipment and identify places at home to exercise safely. The testing equipment includes a blood pressure monitor for measuring resting blood pressure and heart rate, a pulse oximeter for the heart rate recovery test, a hand dynamometer for the grip strength test, and two cones and a tape measure for the Short Physical Performance Battery and the Timed Up and Go tests.

All physical outcomes will be performed by assessors who are trained to administer the teleassessments via Zoom based on standardized protocols. All data from the teleassessments will be entered directly into REDCap. All self-report outcomes will be collected through electronic questionnaire packets delivered via REDCap. All items of the questionnaire packets are set as must-provide-value so participants are required to answer before submission to prevent data missingness. Each questionnaire packet is also set to be delivered to participants three times, separated by 3 days, if it is not completed. A follow-up phone call will be made if participants do not complete the packet after 7 days to ensure participants receive the packet and remind them to complete it within the next 3 days. Randomization will not take place until the the baseline teleassessments and questionnaire packet are completed.

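### Barriers to physical activity are tested as a mediator but measured only before randomization, and the protocol's three mediator lists disagree

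*Protocol article*

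**What the plan says.** Three places in the protocol article define the mediators.

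- **Objectives {7}, tertiary aim.** The study will "explore the role of group cohesion, instructor support, exercise self-efficacy, exercise self-regulation, social support for exercise, and outcome expectations for exercise as mediating variables". That is six variables, with no method named.
- **Outcomes {12}, Table 2.** The mediator block has seven rows: those six plus program adherence, defined as "Percentage of # of attended eM2M sessions". Group cohesion and instructor support are collected at 12 weeks only. Self-efficacy, self-regulation, outcome expectations and social support are collected at baseline and 12 weeks. The row "Barriers in Physical Activity Questionnaire [63]" is not in this block; its role is covariate and its only time point is baseline.
- **Secondary analysis.** "We will examine barriers in physical activity as well as the four Social Cognitive Theory constructs" (self-efficacy, goal-setting, outcome expectancies and social support) are to be examined "as mediating variables between the intervention and the outcomes using the product of coefficients test". That is five variables, and it is the only mediation method the article states.

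On timing, the Interventions section says "Enrolled participants who complete baseline assessments will be randomly assigned to" one of the two arms, and Plans for assessment and collection of outcomes {18a} holds randomization back until the "baseline teleassessments and questionnaire packet are completed". The Interventions section also keeps waitlist participants at their usual activities for the 12 weeks and offers them an eM2M program only afterwards.

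**The concern.** A product-of-coefficients test multiplies path *a* (the effect of assignment on the mediator) by path *b* (the association of the mediator with the outcome, given assignment). Path *a* requires the mediator to be measured after assignment and in both arms.

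Barriers fail the first requirement. The test would run and give a number, but it could not detect mediation through barriers even if the program did lower them. A null result could then be reported as evidence that barriers are not a mechanism. That would matter to this trial, whose rationale is the removal of barriers to exercise.

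Group cohesion, instructor support and attendance raise a different question. They are called mediators, but they describe experience of a class that the waitlist arm does not attend during the comparison. The analysis section is silent on them. A reader cannot tell which mediators are prespecified, or how these three would be handled.

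**Working it through.** The protocol gives no figure for the mediation analysis, so there is none to reproduce. The check sets the lists side by side and then looks at path *a* for each kind of variable.

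**1. The lists.** Goal-setting is taken as self-regulation, because Table 2 measures self-regulation with a goal-setting scale.

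| Variable | Objectives {7} | Table 2 mediator block | Secondary analysis | Collected (Table 2) |
|---|---|---|---|---|
| Self-efficacy | yes | yes | yes | baseline, 12 weeks |
| Self-regulation / goal-setting | yes | yes | yes | baseline, 12 weeks |
| Outcome expectations | yes | yes | yes | baseline, 12 weeks |
| Social support | yes | yes | yes | baseline, 12 weeks |
| Group cohesion | yes | yes | no | 12 weeks |
| Instructor support | yes | yes | no | 12 weeks |
| Attendance | no | yes | no | intervention period |
| Barriers | no | no (covariate) | yes | baseline |
| **Count** | **6** | **7** | **5** | |

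Four variables appear in all three lists, and all four are measured before and after the intervention.

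**2. Barriers.** With *M* measured before assignment *T*, randomization makes *T* independent of *M*. Hence E(*a*) = E(*M* | eM2M) − E(*M* | waitlist) = 0, whatever the program does to barriers later. A simulation of 4,000 trials with 41 per arm (the protocol's 82 completers, split equally) and an assumed *b* of 0.4 gave a mean *a* × *b* of 0.000. Path *a* was significant at the 5% level in 4.3% of runs, close to the nominal rate.

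**3. Cohesion and instructor support.** Path *a* is a between-arm difference. A waitlist participant with no eM2M group or instructor has nothing to rate, so the control value is very likely missing.

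**4. Attendance.** The waitlist arm can be set to zero, so *a* × *b* can be computed. With equal arms, eM2M mean *m* and SD *s*, the correlation of arm with attendance is

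r = (*m*/2) / √(*m*²/4 + *s*²/2).

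The protocol gives no attendance distribution, so *m* = 0.75 and both SDs are assumptions:

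- *s* = 0.12: r = 0.375 / √(0.1406 + 0.0072) = 0.98
- *s* = 0.30: r = 0.375 / √(0.1406 + 0.0450) = 0.87

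All waitlist values are equal, so *b* comes only from differences in attendance among eM2M participants, and those differences are not randomized. To illustrate, suppose eM2M has no effect and a common cause *U* (SD 1) shifts attendance by 0.12 and the outcome by 0.4. Within eM2M, *b* ≈ 0.4/0.12 = 3.33, and *a* ≈ 0.75, so *a* × *b* ≈ 2.5. Simulation gave an indirect effect of +2.52, a direct effect of −2.52 and a total effect of 0.00. The SE of the arm coefficient was 1.08 with attendance in the model and 0.24 without it. These sizes depend on the assumptions.

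**The case against.** The best defence is that the Secondary analysis section applies the product-of-coefficients test to barriers and the four Social Cognitive Theory constructs only. Cohesion and instructor support are named in an exploratory aim without a method, and attendance appears only in Table 2. A condensed article may leave their handling to the full protocol or analysis plan. This stands, and it limits the point.

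A reader might go further and infer that four of the eight variables (barriers, cohesion, instructor support, attendance) cannot be tested by the stated method. The documents do not support that, for three reasons:

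- The stated test is assigned to five variables, and one of them is defective.
- Attendance can be computed with zeros in the waitlist arm, and it varies within eM2M, so it is not an exact copy of the arm indicator. The difficulty is one of interpretation and precision.
- Absence of waitlist data on cohesion and instructor support is inferred from the Interventions section. No text says who receives those questionnaires, and the schedule in Table 3 is not available in the text reviewed.

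None of this rescues barriers. The analysis section says mediating, Table 2 says baseline covariate, and the two statements cannot both be carried out meaningfully. Nor is barriers likely to be a slip for a moderator, since Table 2 names functional mobility and disability type in that role. Leaving detail to an analysis plan does not explain conflicting statements within one document.

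**Conclusion.** The barriers test is wrong as written. One of the five variables given the product-of-coefficients test has an expected path *a* of zero by design. This follows from randomization and from the stated timing, and needs no numerical assumption.

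The conflict among the three lists (six, seven and five variables) is also real. For cohesion and instructor support, a between-arm path very likely lacks a control value; this rests on inference from what the waitlist arm receives. For attendance, a between-arm path would be strongly collinear with arm (correlation about 0.87 to 0.98 under the assumed distributions) and would rest on non-randomized variation within eM2M.

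The consequence is confined to an exploratory tertiary aim. The primary and secondary outcome analyses are unaffected, and the four mediators common to all three lists remain testable.

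**What to change.** 1. In the Secondary analysis section, remove barriers from the mediation test and keep it as the baseline covariate of Table 2. If mediation through barriers is wanted, add the questionnaire to the existing 12-week packet in both arms and list it in Table 2 as a mediator at both time points.
2. Describe group cohesion, instructor support and attendance as process measures, analysed within eM2M as associations with outcome and not as mediators of assignment.
3. Use one mediator list in Objectives {7}, Table 2 and the Secondary analysis section.

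The cost is mainly wording. Cohesion and instructor support are named in the tertiary aim, so relabelling them alters that aim. If this is judged an important amendment, the section on communicating protocol amendments {25} requires prior approval from the funder's program officer. The optional 12-week barriers questionnaire adds one instrument and should be decided early: Trial status puts the start of recruitment in December 2020 and projects the first wave for March 2021, and 12-week barriers not collected from a wave cannot be recovered later.
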